## **Introduction**

In Suriname, Cardiovascular Disease (CVD) is the highest cause of death [1]. Stroke, which is part of CVD, is a major cause of adult disability and the number of stroke survivors in low and middle income countries such as Suriname (LMICs) is projected to rise [2]. Impaired upper (e.g. shoulder mobility) and lower extremity function (e.g. impaired ankle mobility) is common after stroke. Problems with motor control, sensory disturbances (including pain), problems using or understanding language (aphasia), depression, cognitive problems, changes in perception and fatigue syndrome can occur after stroke. These impairments result in decreased aerobic capacity, decreased walking capacity, decreased physical functioning and a deterioration of the quality of life.

It is well known that aerobic capacity is decreased in chronic stroke survivors [3] and that the level of physical activity in this group of patients is not enough to induce health benefits [4], which in turn increase their risk of early mortality and recurrent stroke [5]. Studies show that physical fitness training is a way to modify and improve aerobic capacity after chronic stroke [5, 6]. It is reported that an improvement in physical fitness is associated to an increase in sensorimotor function, improved walking capacity and increased quality of life in chronic stroke survivors [5-7][24]. However, so far, most studies were conducted in a laboratory or hospital setting. For chronic stroke survivors, home-based rehabilitation is a promising alternative to regular center-based stroke rehabilitation [8] especially after hospital- and community-based studies consistently reveal low levels of physical activity for stroke survivors [9, 10]. Literature search documents that the long term training effect and the effective training dose for aerobic capacity after home-based training for chronic stroke survivors is understudied [11]. A study done by Duncan and colleagues in a home-based setting reports significant gains for peak aerobic capacity after progressive home based exercise for patients with subacute stroke [12]. Moore and colleagues studied chronic stroke patients and showed significant increase in physical function, cognition and quality of life after a community-based exercise program[13]. Little is known regarding potentially beneficial effects of supervised home-based exercise training in patients with chronic stroke, warranting further research. [11, 13]

Similarly, impaired upper extremity function (e.g. reduced upper arm function and shoulder pain) is common after stroke and can be positively influenced by rehabilitation exercises [14]. In most high income countries, patients with chronic stroke keep visiting their physiotherapists for upper limb rehabilitation in order to maintain as much as possible the function and flexibility in the paralyzed arm, while also preventing or treating shoulder pain. In Suriname, patients with chronic stroke do not receive any further physiotherapy treatment after the acute phase of stroke. The enhancement of the functionality of the upper limb is a core element of stroke rehabilitation to maximize the effect on patient outcomes and decrease disability and is still considered effective in the chronic phase [15, 16]. Unfortunately, the financial resources are not in place in Suriname for patients in the chronic patients with stroke, making it unable for them to pay for further necessary treatments.

Telerehabilitation is a good way to reduce costs in a setting where the financial resources are low. It is defined as the ability to provide distance support, evaluation and intervention to persons who are disabled via telecommunication [17]. Literature reports [18, 19] some positive effects of telephone interviews on the motor function and quality of life in chronic stroke patients, but the effect on physical fitness level and adherence to a physical fitness program is understudied.

All the above summarized scientific evidence results from research in high income economies and the need for research in the setting of LMICs has already been outlined [20]. Reasons for the lack of trials in LMICs probably include funding difficulties and paucity in skilled personnel for research, but local conditions and characteristics of patients with stroke in these areas are equally important [21].

We can assume that patients in LMICs will experience more barriers towards participation in clinical exercise programs. Therefore the study designs adopted in previous research might not entirely suit the multi-ethnic

population of the LMIC of Suriname. Bringing an intervention as close as possible to the patient, while keeping the expenses low with help from emerging and relatively cheap technologies, seems more important in the setting of Suriname in order to avoid patients dropping out. We believe a home based physical fitness and rehabilitation program might be an effective way to stimulate chronic stroke survivors in Suriname to build long lasting healthy exercise habits resulting in long term positive effects on aerobic capacity, health related quality of life, quality of gait, and upper limb functionality.

## **Objectives**

The main objective of this research is to investigate the short and longer term effects of 8 weeks of a tele-supervised home-based exercise and physiotherapy program on **aerobic capacity, quality of gait and health related quality of life** in people with chronic ischemic stroke.

At first, the feasibility and cost-effectiveness of the program will be evaluated.

Secondly, possible underlying determinants for aerobic capacity and the training effect on aerobic capacity will be investigated.

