## **Methods**

**Study design:** The proposed project is a prospective, single blind, randomized controlled intervention trial in patients with chronic stroke.

**Setting:** Patients will be recruited from the Rehabilitation Center Paramaribo; from the community and from the union for people after stroke.

**Patient population:** Patients with chronic ischemic stroke and following the inclusion criteria can be included in the study:

Inclusion criteria:

- ability to give informed consent
- ability to understand measurement procedures defined as MMSE >24 [22]
- last stroke >6 months ago
  
- mild to moderate stroke deficit defined by Fugl Meyer test score of 27 to 90 for upper and lower extremities [12]
- FAC  $\geq 3$
- medical clearance to participate in a moderate exercise program
- living at home and having a minimum of 5 stairs at home

Exclusion criteria:

- serious cardiac condition [22]
- other serious end organ damage
- other neurological deficits leading to disability
- uncontrolled blood pressure (systolic pressure >140, diastolic pressure >90) [22]

**Statistical power and sample size:** Sample size calculation was performed with PS Power and Sample Size Calculation (<http://biostat.mc.vanderbilt.edu/PowerSampleSize>) The sample size for the two-sample case (training versus control) was estimated on the basis of the results of Moore et al [13] for effect of exercise on cardiorespiratory capacity. In this study the response for peak VO2 within each subject group was normally distributed with standard deviation 3.4. If the true difference in the experimental and control means is 3.0, we will need to study 17 experimental subjects and 17 control subjects to be able to reject the null hypothesis that the

population means of the experimental and control groups are equal with probability (power) 0.8. The Type I error probability associated with this test of this null hypothesis is 0.05. We chose to aim for a sample size of 20 patients per group taking drop outs into account.

Participant stratification will be balanced for gender because men tend to have higher aerobic capacity and muscle strength than women. The participants will be assigned randomly to a group by a computer program ([www.randomization.com](http://www.randomization.com)). Informed consent (appendix I) must be signed by every participant.

**Intervention** There is an intervention group (physical fitness exercise) and a control group (usual care) [13].

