The intervention will be provided by a physical therapist for 4 weeks (3 times/wk, 70 minutes). This duration of intervention was selected because it improved the cardiorespiratory function of chronic stroke survivors [11]. After that a telephone supervised method for 4 weeks is done to monitor if the patient is continuing the exercise program at a given intensity. To progress in cardiorespiratory fitness level a pedometer based step goal [4] will be set.

**Measurements:** Following measurements and paper and pencil surveys will be undertaken in order to evaluate the subjects at baseline at 4 weeks, 8 weeks and 5 months:

**Anthropometric characteristics** weight, height, body mass index, % fat (bio-electrical impedance) and waist and hip circumference will be measured.

**Exercise tolerance** (peak VO2) will be assessed by submaximal graded cardiopulmonary exercise testing (CPET) with breath-by-breath analysis (Jaeger Oxycon Mobile®) on a cycle ergometer. Submaximal fitness parameters will include 1st and 2nd ventilatory thresholds, oxygen uptake efficiency slope and the VE/VCO2-slope. We will use a graded protocol in which the patient starts with a 10 min warming-up session at zero workload [12] followed by workload increments of 10W every minute until maximal effort is reached or symptoms appear [3, 12]. Submaximal effort is defined as the inability to continue cycling at a pace of 50-60 revolutions per minute due to shortness of breath and/or leg fatigue.

**Hemodynamic and vascular function at rest** will be non-invasively assessed by means of the Nexfin device which will provide resting systolic and diastolic blood pressure, cardiac output, stroke volume and systemic vascular resistance. Furthermore brachial ankle index will be determined by blood pressure measurements at non-paretic upper arm and ankle. Finally arterial stiffness will be evaluated by use of the Arteriograph.

**Lung function** will be evaluated by vital capacity and forced expiratory volume in 1 second measured before starting the CPET, using the same equipment for breath by breath analysis.

**Habitual physical activity** will be objectively assessed during 7 consecutive days and nights by means of the physical activity device that will also be used to guide the intervention, designed to be worn constantly around the upper arm (like a watch) [23].

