**Walking endurance** will be tested with the 6-minute walk test. This test is a reliable submaximal test of cardiorespiratory capacity in people with stroke [24, 25].

**Quality of gait** will be defined by spatiotemporal parameters such as step length, stride length, step width, paretic stance time and gait speed. These parameters will be recorded in a human movement laboratory by two camera's (Panasonic HDC-TM900 3 MOS HD camcorder and Canon powershot SX40 HS) which capture data that will be analyzed with Kinovea, an open source video tool.

**The manual muscle testing (hand-held dynamometer), and handgrip strength test** will be used to evaluate upper limb function [26-29] and knee extensor strength [30, 31].

**Balance** will be evaluated by the Berg balance scale, which consists of 14 tasks and a score range of 0-56 [32].

**Health related quality of life** will be evaluated using the SF-12 questionnaire [33-35].

**Disabilities of arm, shoulder and hand** will be evaluated by means of the DASH questionnaire [36, 37].

**Exercise self-efficacy** will be evaluated by use of the Dutch translation of the Exercise Self-Efficacy Scale (ESES) [38].

**Database management** will be performed by use of Microsoft Excel 10.0. All data will be anonymized before being processed. Repeated measures ANOVA will be performed by use of SPSS statistical software in order to reveal differences between control and intervention groups regarding the primary and secondary outcome measures.

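### The main objective gives three outcome domains equal weight, but the 0.05 error rate and the sample size cover one peak VO2 comparison, and no primary outcome or time point is named

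*Protocol*

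**What the plan says.** Four places in the Protocol bear on this.

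- **Objectives.** The outcomes that the main objective names are "aerobic capacity, quality of gait and health related quality of life". These three domains stand side by side. The stated purpose, "investigate the short and longer term effects of 8 weeks of a tele-supervised home-based exercise and physiotherapy program", covers more than one horizon, and no lead time point is given.
- **Methods, Statistical power and sample size.** The calculation rests on earlier trial results "for effect of exercise on cardiorespiratory capacity". It uses peak VO2 with SD 3.4 and a difference of 3.0, and arrives at 17 per group, raised to 20 for dropouts. The error rate is tied to that one comparison: "The Type I error probability associated with this test of this null hypothesis is 0.05". No visit is named.
- **Methods, Measurements.** Staff will "evaluate the subjects at baseline at 4 weeks, 8 weeks and 5 months", which makes three visits after baseline. Gait is described by examples: "step length, stride length, step width, paretic stance time and gait speed". Quality of life is the SF-12.
- **Methods, Database management.** Repeated measures ANOVA is to compare the groups "regarding the primary and secondary outcome measures". Neither set is listed anywhere in the protocol.

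**The concern.** The objective has three domains over more than one horizon, the sizing has one variable at an unnamed time, and the analysis refers to a primary set that does not exist in the text. A reader cannot tell from the protocol which result decides the main question.

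Two things are at stake. First, the 0.05 describes the whole trial only if one test decides it. With three domains of equal standing and no rule for combining them, the error rate of the overall conclusion is not fixed. Second, no effect size or SD is given for gait or for SF-12, so two of the three domains in the main objective have no power basis.

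**Working it through.** **Inputs.** Three domains (Objectives). Difference 3.0, SD 3.4, alpha 0.05, power 0.8, 17 per group, 20 with dropouts (Statistical power and sample size). The documents give no correlation between outcomes; the values below are assumptions.

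**1. The plan's own figure.** The normal approximation per group is n = 2 × [SD × (z for alpha + z for power) / difference]².

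- Two-sided 0.05: 2 × [3.4 × (1.960 + 0.842) / 3.0]² = 20.2, so 21. The exact t-test needs 22.
- One-sided 0.05: 16 by the normal approximation. The t-based iteration gives 16.7, so 17.

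The stated 17 is therefore reproduced only with a one-sided test. The sidedness is not stated, but the null hypothesis ("population means of the experimental and control groups are equal with probability (power) 0.8") is one of equality and implies two sides. Exact t-test power:

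| Evaluable per group | Two-sided 0.05 | One-sided 0.05 |
|---|---|---|
| 17 | 0.70 | 0.81 |
| 20 | 0.78 | 0.86 |
| 22 | 0.82 | 0.89 |

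**2. Error rate if any one domain is enough.** With one test per domain at 0.05 and no true effect, the chance of at least one false positive for independent tests is 1 − 0.95³ = 0.143. For correlated two-sided tests it was simulated from equicorrelated normal statistics (400,000 draws):

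| Assumed correlation between domains | Chance of at least one false positive |
|---|---|
| 0 | 14.3% |
| 0.3 | 13.5% |
| 0.5 | 12.5% |
| 0.7 | 10.9% |

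Even at 0.7 this is more than twice 5%.

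**3. If all three must succeed.** The error rate does not inflate. The chance of joint success cannot exceed the power for peak VO2 alone and is lower unless the other two are almost certain to succeed. As an illustration only, three independent tests with 0.80 power each would succeed together with probability 0.8³ = 0.51. The actual figure cannot be computed, because nothing is given for gait or SF-12.

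**4. If the error rate were split equally.** At 0.05/3 = 0.0167, two-sided, peak VO2 needs 29 evaluable per group (exact t). Power is 0.53 with 17 and 0.61 with 20. Three primary outcomes with a split error rate are therefore not affordable at the planned size, while one primary outcome leaves the 0.05 intact.

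**The case against.** The best defence is that the protocol never calls the three domains jointly primary. It says it will investigate effects, sets no success rule, and distinguishes primary from secondary outcomes, so some order was intended. The sample size and one of the further aims both point to aerobic capacity as the lead. Testing order, division of the error rate and handling of repeated visits are commonly left to a statistical analysis plan, which may exist.

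Much of this stands. A reader might infer that the protocol declares three co-primary outcomes; it does not, and that would be an interpretation of the objective. A reader might also infer that the headline result will be chosen after the data are seen. That cannot be said without knowing what an analysis plan fixes.

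Two larger error figures are also tempting. Counting peak VO2, five gait parameters and one SF-12 score as seven tests gives 1 − 0.95⁷ = 30% if independent, or 23% at an assumed common correlation of 0.5. But the gait parameters are offered as examples of a domain, and nothing says that each is a separate test carrying the main claim. Counting three visits for each of three domains gives 1 − 0.95⁹ = 37% if independent. But repeated measures ANOVA can give one group-by-time test per outcome, so visits add error only if each is tested separately, which the protocol does not say.

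What does not stand is leaving the primary outcome and its time point to another document. The sample size depends on them, and the protocol's own analysis sentence presupposes that they have been named.

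**Conclusion.** The point holds as a mismatch between the main objective, the sizing and the analysis paragraph. The supportable size is a family-wise error of 14% for three independent tests and about 11% to 14% at correlations of 0.7 to 0.3. It is conditional on one unadjusted test per domain and on success in any one domain being enough. Under an all-three rule there is no inflation, but the stated 0.8 does not describe the trial. Either way the protocol leaves open which rule applies.

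The data would remain usable, and the defect can be removed by wording. It should be corrected, but it does not invalidate the design.

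**What to change.** In Objectives and in the analysis paragraph, name peak VO2 as the single primary outcome, since it is the only one with a power basis, at one stated time point. Eight weeks, the end of the programme, is the natural choice, although the sample size paragraph does not itself point to a visit. Say which comparison from the repeated measures model is the primary one.

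Make gait, SF-12 and the other visits secondary, with 5 months kept as the stated longer-term result. Either report these as estimates with 95% confidence intervals, or test them in a fixed order written down beforehand with one gait parameter named in advance. Which parameter is for the investigators to choose; the documents do not settle it.

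Restate the power alongside. A two-sided 0.05 test should not be described as matching 17 per group, because its power is about 0.70 at 17 and 0.78 at 20 evaluable. The protocol should state the sidedness and then either the lower power or the 22 evaluable per group that 0.8 requires.

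Naming one primary outcome costs wording only and adds no assessments; recruiting to 22 evaluable per group would cost more patients. The downside is that gait and quality of life can no longer carry the main claim alone.

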### Time Planning:

Start research project: March 1st 2016

Anticipated end of research project: March 31th 2017

**There will be no charges for the patient and there will also be no extra costs for the rehabilitation center as all measurements will be performed by staff and equipment belonging to the research group.**

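### Cost-effectiveness is a stated objective, but the protocol specifies no collection of cost, resource use or health-care use in either arm; feasibility is only partly covered

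*Protocol*

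**What the plan says.** After the main objective, the Objectives section adds: "At first, the feasibility and cost-effectiveness of the program will be evaluated".

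The measurement list in Methods opens with "Following measurements and paper and pencil surveys will be undertaken in order to evaluate the subjects", and sets four time points: baseline, weeks 4 and 8, and month 5. It covers body composition, the cycle exercise test, resting haemodynamics and arterial stiffness, lung function, habitual activity, the six-minute walk, gait, strength, balance, quality of life, arm disability and exercise self-efficacy. Quality of life "will be evaluated using the SF-12 questionnaire".

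Delivery is described separately, also in Methods: "The intervention will be provided by a physical therapist for 4 weeks (3 times/wk, 70 minutes"). In weeks 5 to 8, "a telephone supervised method for 4 weeks is done to monitor if the patient is continuing the exercise program at a given intensity", and a step goal is set by pedometer. Habitual activity is "objectively assessed during 7 consecutive days and nights by means of the physical activity device that will also be used to guide the intervention".

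The comparator is usual care, which the protocol explains means no exercise programme. The one analysis named is a repeated measures ANOVA comparing the groups. The remaining statement about money, in Time Planning, is that patients are not charged, with this further assurance: "there will also be no extra costs for the rehabilitation center as all measurements will be performed by staff and equipment belonging to the research" [team].

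**The concern.** A cost-effectiveness evaluation needs two things from each arm: an effect and a cost. The protocol collects the first in detail and specifies nothing for the second. This is a gap in data collection. A later analysis plan can choose a perspective, unit prices and a ratio, but it cannot analyse resource use that nobody was asked to record.

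Cost is also central to the argument for the trial. The Introduction presents remote supervision as a way to save money where patients cannot pay for continued physiotherapy. A reader in that setting will want to know what the programme cost to deliver. If the plan is followed as written, any answer would rest on assumed costs.

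Feasibility has a lesser version of the same problem. The protocol names no feasibility outcome or criterion, and attendance at the therapist-led sessions, which is the most direct indicator for weeks 1 to 4, is not among the listed data.

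**Working it through.** No figure in the protocol is in dispute, so the check compares the objective with the data planned and then asks how much cost information the schedule alone could supply.

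**1. What the objective needs and what is specified**

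| Needed | Specified in the protocol |
|---|---|
| Effect, both arms | Yes: peak VO2, SF-12 and the other listed outcomes at four time points |
| Therapist time delivered | Planned sessions only; no record of delivery specified |
| Travel time | Not specified |
| Telephone time | Four weeks of supervision; number and length of calls not given |
| Devices | Pedometer and activity device mentioned; no costing specified |
| Health-care use, both arms | Not specified |
| Session attendance, weeks 1 to 4 | Not listed as recorded |
| Adherence, weeks 5 to 8 | Partly: telephone monitoring; how calls are recorded is not stated |
| Activity level | Yes: seven-day device measurement |
| Retention | Can be counted from drop-outs |

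**2. The ratio.** With costs C and effects E in the intervention (I) and control (C) arms, the usual summary is

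(C_I − C_C) / (E_I − E_C).

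The denominator can be estimated from the planned data. Neither term of the numerator can.

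**3. What the schedule alone would give.** Inputs from Methods: 3 sessions per week, 4 weeks, 70 minutes per session, 20 patients per group.

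- Sessions per patient: 3 × 4 = 12.
- Planned therapist time per patient: 12 × 70 = 840 minutes = 14 hours.
- Planned therapist time for the group, assuming one patient per session: 20 × 14 = 280 hours.

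This is intended contact time. It leaves out travel, and the calls cannot be added because their number and length are not stated.

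**4. How far delivery could differ from plan.** The protocol gives no attendance figure, so take 60% to 100% purely as an illustration.

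- At 60%: 0.60 × 14 = 8.4 hours per patient; 20 × 8.4 = 168 hours in all.
- At 100%: 14 hours per patient; 280 hours in all.

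Over that assumed range the largest identifiable cost item varies by 280 − 168 = 112 hours. Without an attendance record the trial could not say where in the range it fell.

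**5. The control arm.** No exercise programme means a programme cost of zero. It does not mean zero health-care use over the five months, and that is not measured in either arm.

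**The case against.** Several points can fairly be made on the other side.

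*The list concerns assessments of the patient.* Therapist hours, call minutes and purchases are programme inputs, and their absence from such a list does not show that no record will be kept. This stands. A reader might infer that therapist time will go unrecorded; the protocol does not say so. The supportable statement is that recording is not specified.

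*A cost can be built from the plan.* From the provider's side, 14 hours per patient set against a comparator with no programme gives an incremental programme cost once prices are attached. This stands in part. Such a figure describes intended delivery, omits the calls and travel, and says nothing about health-care use.

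*Since patients are not charged, a reader might infer that costs cannot be recovered later.* The documents do not support that. Time Planning deals with who pays and who performs the measurements; payroll, travel or purchase records may exist with the provider. Their existence is simply not planned for.

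*Feasibility is not empty.* A reader might infer that feasibility cannot be assessed, or only through drop-out. Methods contradicts this: the telephone contact monitors whether exercise continues and at what intensity, a step goal is set, and activity is measured objectively. This objection stands in full against that inference.

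*Adverse events.* The objective does not define feasibility by falls or other events. Recording them is sensible but optional for this point.

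*Perspective, prices and choice of ratio belong in an analysis or economic plan.* Agreed, and their absence from the protocol is no part of this point.

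**Conclusion.** The point holds in a limited form. The protocol sets a cost-effectiveness objective but specifies no collection of cost, resource use or health-care use in either arm. The most that could be produced is an assumed planned-delivery programme cost of 14 therapist hours per patient plus an unstated quantity of telephone contact. No cost-effectiveness result could rest on trial data.

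Feasibility can be answered in part, through adherence in weeks 5 to 8, device-measured activity and retention. Session attendance in weeks 1 to 4 is the missing piece.

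The conclusion rests on reading the protocol as the complete statement of data to be collected. If case report forms or provider records already capture delivery and health-care use, the gap is one of documentation. The 60% to 100% attendance range is illustrative and the conclusion does not depend on it. The main objective, the sample size and the comparison of clinical outcomes are untouched, so this is something the sponsor should correct, but it does not threaten the trial's central result.

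**What to change.** Preferred: add two items to Methods.

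- A short per-patient delivery log kept by the treating therapist: sessions attended, therapist and travel minutes, number and minutes of calls, and devices issued. Falls and other adverse events can be added if the sponsor wishes.
- A brief self-completed health-care-use question for both arms, added to the existing paper surveys at the four time points. The trial is described as single blind, and answers could reveal allocation, so someone other than the blinded assessor should hand out and collect this sheet.

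Report incremental cost descriptively, and state that feasibility will be measured by attendance, adherence and retention.

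Alternative: remove cost-effectiveness from the Objectives and limit the claim to feasibility, measured in the same three ways. Attendance would still have to be recorded.

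The cost is a small amount of record keeping and one extra survey item at visits already planned. The cost result will be imprecise with 20 patients per group and should be presented as such.
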